### Research participants

*Adolescent participants* for Phase 1 (formative research) will be recruited from among HIV-positive patients aged 12–17 years who receive ART at NHP, along with their primary caregivers. All of these patients were perinatally infected. Adolescent participants for Phase 2 (RCT) will be recruited from the same NHP population. To be enrolled in either phase, adolescents must be on ART, in care at NHP (or graduated from NHP care in the case of older youth at adult OPCs), agree to follow study procedures, provide informed assent, and have their caregiver provide written informed consent. For the RCT, additional inclusion criteria will apply; participants in Phase 1 activities will be eligible to participate in the Phase 2 RCT. Adolescents must also expect to remain in care at the NHP for seven months minimum and be identified as having adherence challenges, defined by: detectable VL, CD4 < 700 in the last six months, or decline in CD4 in the last six months. Adolescents who are aged < 12 years or > 18 years, live outside the clinic catchment area, decline to provide informed assent, have a caregiver who declines to provide consent, or have a mental health condition sufficiently serious that they cannot understand informed assent, including the voluntary nature of participation, will be excluded.

*Adolescent participants* aged ≥ 18 years for Phase 1 (formative research) will be recruited from among HIV+ patients aged 18–21 years who have transitioned to care at OPCs in Hanoi. *Caregiver participants* for Phase 1 (formative research) must be identified as the child’s primary caregiver and will be recruited along with the adolescent patients at NHP selected for the IDIs or FGDs. *Clinician participants* from the Infectious Disease Clinic at NHP will be recruited for participation in Phase 1 (formative research) and all clinicians there will be eligible.

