### General approach

We will calculate descriptive statistics for all study variables (means, ranges, standard deviations, percent data missing, and frequencies, percentages for categorical variables). For adherence, a non-opening for a scheduled dose will be considered a non-adherent dose. Repeated openings within the same scheduled dose time will be excluded. Outcomes will not be imputed for patients who drop out. Patients who drop out before randomization will be excluded in experimental analyses. Sociodemographic and clinical characteristics from baseline will be compared between those randomized and those not randomized to assess representativeness of the final analytic sample, using Cochran Mantel–Haenszel χ^2^ tests for categorical variables and Student’s *t* tests for continuous variables. After randomization, we will compare dropout rates and characteristics of patients who drop out between study arms to assess potential for bias using the same statistical tests. All randomized participants will be included in analyses. We will perform both intention-to-treat (ITT) and per-protocol analyses.

For the main dichotomous outcome (% ≥ 95% adherence after the intervention [Month 7]), risk differences and 95% confidence intervals will be calculated. UDVL will be similarly treated as a secondary dichotomous outcome. We will then construct multivariate regression models to adjust for key baseline variables such as gender, using high adherence as the outcome, and intervention group as the primary predictor. Other variables found to be significantly associated with high adherence in bivariate logistic models will be added using forward-stepwise and forced entry techniques. We will also conduct stratified analyses based on gender and other attributes, although we may only have statistical power to detect trends. For continuous outcomes (change in adherence and CD4 count), we will use paired t-tests and General Linear Models to test for differences before and after intervention, then use similar multivariate approaches as described above. To examine interrelationships among adherence and the constructs of our theoretical model, stigma, and other psychosocial measures, we will generate bivariate Pearson correlations and conduct exploratory path analysis.

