### Sample size and power considerations

The formative component in Phase 1 will include: IDIs with adolescent/caregiver dyads (20 dyads, for a total of 40 IDIs); one FGD with 8–10 clinicians; one FGD with 8–10 caregivers; up to six FGDs with adolescent patients (three with girls, three with boys, with 8–10 participants each; maximum 60 total participants); 20 IDIs with older adolescents aged ≥ 18 years receiving care at adult OPCs (10 with young women, 10 with young men). Total maximum qualitative participants will be 140: 40 IDIs with NHP adolescent patients/caregivers; 10 clinicians in FGD, 10 caregivers in FGD, 60 FGD participants aged 12–15 years; 20 IDI participants aged ≥ 18 years. These numbers are adequate to elicit a range of experiences of youth, their caregivers, and clinicians.

We have powered the RCT in Phase 2 to be able to detect meaningful changes in optimal adherence. We will recruit 80 adolescent patients, 40 per study arm, which will provide a minimum of 80% power at a two-sided alpha of *p* = 0.05 to detect specified differences in adherence between the two arms after intervention. Our estimates of outcome differences are based on our findings from our earlier CATS study with Chinese adults, in which we found that proportions achieving ≥ 95% adherence were 87.3% versus 51.8%, in intervention versus control patients after six months of the intervention [43]. We will have a minimum of 80% power to detect down to a 29 percentage-point difference in proportions achieving ≥ 95% adherence between arms after the intervention.

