## Operational issues and discussion

In addition to enhancing understanding of the issues adolescent patients face in order to better tailor support strategies for ART adherence, SAAV is designed to add to our understanding of the feasibility and effectiveness of wireless technology to improve adherence and viral suppression. At the time of submission of this protocol, the team was completing analysis of the Phase 1 qualitative data and enrolling patients for the RCT. During the preparatory period, the team encountered several issues that bear on the conduct of the study and which may be informative to other researchers involved in similar work with adolescents.*Challenges of interviewing adolescents with caregiver present*. We had hoped to interview adolescents (both for the IDIs in the formative phase and the RCT) separately from their caregivers so that youth could be more comfortable in expressing themselves freely with study staff, but in the formative phase, we have encountered the situation that some caregivers prefer to stay in the interview room with their child. We realize that the study team cannot insist on separation, but we believe that some interview and survey data may be affected by a child’s eagerness to please a caregiver (who is present). For the RCT, the study team has devised several strategies to encourage (though never force) caregivers to wait outside the interview room. In all cases, we are documenting whether the caregiver is present for each study activity, in addition to noting how the child and caregiver related in cases when both were present.*Reticence of many adolescents in formative phase*. We discovered that many of the adolescents in the IDIs were reluctant to talk in much detail about their medication-taking behavior, whether a caregiver was present or not. This finding is similar to our experience with adolescents of similar age in China [63]. Our local interviewers devised a series of icebreakers and other games to try to put the adolescents at ease, which has seemed to elicit some additional participation. Exploring adolescents’ general adherence challenges via peer engagement in a FGD format might be another beneficial strategy, perhaps with multiple meetings which could foster trust with facilitators and among participants.*Increasing independence of older adolescents*. We are learning that the increasing independence of older youth in our study population has very real implications for the conduct of the research study. Many of the older adolescent participants (aged 15–17 years) regularly travel to the clinic on their own, which is less costly for the family, but makes it challenging to obtain caregiver consent and therefore to enroll these older youth in study activities. We recently obtained IRB approval to obtain verbal consent from caregivers by phone which we expect to facilitate RCT recruitment.*WPC issues*. While many details had been worked out with the WPC vendor in advance and specified in the contract, additional features and services were requested during the preparatory period related to the use of Vietnamese language messages and specifics of the adherence report used in monthly counseling. These issues were resolved after discussion with the vendor and consultation with our local implementing partners who are experienced in using Vietnamese language with wireless technologies. Researchers should recognize that some logistics and technical details of any technology may be complex when used in global settings; teams should plan to allocate time for working out such matters whenever partnering with any vendor. Our team has had similar experiences with prior technology vendors.*Identification of adolescents at high risk of low adherence*. The team is fully cognizant of the importance of using systematic criteria for identifying adolescents at risk of low adherence as eligible for the RCT. Despite limited preliminary VL data available to the team during the design phase of the study, during the set-up period, we learned that standard of care annual VLs are rarely obtained in northern Vietnam due to cost, so we relied on recent CD4 history (past three and six months) as the main proxies for low adherence risk. Although this not ideal, we were able to adjust the project budget in order to pay for baseline VL tests for all RCT participants which will help to contextualize our adherence findings. Similar future studies should anticipate such issues and include ample funding for dedicated lab testing.*Incorporation into study of older adolescents who have already transitioned to adult care*. Those adolescents who have already transitioned to adult OPC care (aged 18–21 years) likely also experienced adherence challenges and perhaps even greater challenges than those of the NHP age group who are still in pediatric care. These youth are difficult to track in Vietnam, however, due in large part to frequent switching of cell phone numbers related to cell provider promotions. Although this was not explicitly part of our original study objectives, we thought it important to take advantage of our opportunity partnering with the NHP clinic to track some older adolescents who have recently graduated to adult care in order to learn about their experiences. We were able to modify the protocol to include additional IDIs with these older youth in the formative phase via a protocol amendment. We expect that findings from these interviews will provide valuable insight into the pediatric/adolescent HIV care continuum at the critical point of the transition to adult care.

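### The planned between-arm comparison of undetectable viral load at Month 7 does not condition on baseline viral load, which is measured in everyone before randomisation; the cost is some precision on a secondary outcome

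*Protocol article*

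**What the plan says.** All references are to the protocol article.

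- **Entry.** Research participants defines adherence challenges for the RCT by any one of three conditions: "detectable VL, CD4 < 700 in the last six months, or decline in CD4 in the last six months". Operational issues and discussion explains that routine VL tests were seldom done because of cost, so recent CD4 history served as the main proxy.
- **Baseline VL.** RCT data collection procedures has every participant give blood for VL at Month 1, before randomisation, and again at Month 7. Operational issues and discussion gives one purpose for the baseline tests: the budget was changed to "pay for baseline VL tests for all RCT participants which will help to contextualize our adherence findings".
- **Randomisation.** Pre-intervention period and randomization (Month 1) stratifies on Month 1 adherence, at or above versus below 95%, and on nothing else.
- **Outcome list.** Clinical markers lists the Month 7 UDVL percentage, a baseline-to-endline comparison and an arm comparison. Analytic approach (Specific Aim 4) adds that results will also be shown by pre-randomisation adherence stratum, and calls the analysis non-confirmatory.
- **Method.** General approach gives the main binary outcome, high adherence at Month 7, a risk difference with a 95% confidence interval, and then says "UDVL will be similarly treated as a secondary dichotomous outcome". The regression models that follow take high adherence as the outcome. Gender is the only covariate named, and further covariates are added if they are associated with high adherence.

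**The concern.** An adolescent can enter on CD4 alone while already undetectable. For that participant the Month 7 outcome records whether suppression was kept; for one who enters detectable, it records whether suppression was gained. Baseline VL status is likely to be a strong predictor of Month 7 status, since it is the same marker measured about six months earlier.

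The plan pays for that predictor in every participant but does not bring it into the comparison of arms. Two things are at stake. With 40 per arm, the groups can differ by chance in their share undetectable at entry, and that difference carries through to the crude Month 7 contrast. In addition, variation that baseline status could explain stays in the standard error. There is also a point of interpretation: one pooled percentage does not show separately how many kept and how many gained suppression, and planners of the larger study mentioned under Dissemination would want both rates.

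**Working it through.** **1. The plan's own figure.** The only power statement concerns adherence. The inputs from Sample size and power considerations are "We will recruit 80 adolescent patients, 40 per study arm", "a two-sided alpha of *p* = 0.05", "which will provide a minimum of 80% power", and reference rates given as "proportions achieving ≥ 95% adherence were 87.3% versus 51.8%, in intervention versus control patients". The claim is power to "detect down to a 29 percentage-point difference in proportions achieving ≥ 95% adherence between arms after the intervention".

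Put the control rate at 51.8% and the intervention rate at 80.8%, and use the pooled-variance normal approximation. The mean rate is 0.663.
- Null SE = √(2 × 0.663 × 0.337 / 40) = 0.1057
- Alternative SE = √[(0.518 × 0.482 + 0.808 × 0.192) / 40] = 0.1006
- Power = Φ[(0.29 − 1.96 × 0.1057) / 0.1006] = Φ(0.823) = 79.5%

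The figure reproduces within rounding. No power or precision is stated for UDVL.

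**2. Precision of the UDVL difference.** The article gives no UDVL rates, so three quantities are assumed:
- u, the share undetectable at baseline: 0.3 to 0.9
- a, Month 7 UDVL among those undetectable at baseline: 0.85 to 0.95
- b, Month 7 UDVL among those detectable at baseline: 0.3 to 0.5

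With 40 per arm and no treatment effect:
- Overall rate m = u·a + (1 − u)·b
- Crude SE = √[2m(1 − m)/40]
- Share of variance explained R² = u(1 − u)(a − b)² / [m(1 − m)]
- SE conditioning on baseline VL status = crude SE × √(1 − R²)

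Worked case, u = 0.7, a = 0.95, b = 0.3:
- m = 0.665 + 0.09 = 0.755, and m(1 − m) = 0.1850
- R² = 0.21 × 0.4225 / 0.1850 = 0.480
- Crude SE = √(2 × 0.1850/40) = 0.0962; conditional SE = 0.0962 × √0.520 = 0.0694
- The 95% half-width falls from 18.8 to 13.6 points.

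| u | a | b | R² | Crude SE (points) | Conditional SE (points) | Reduction |
|---|---|---|---|---|---|---|
| 0.3 | 0.95 | 0.3 | 0.355 | 11.18 | 8.98 | 20% |
| 0.5 | 0.95 | 0.3 | 0.451 | 10.83 | 8.02 | 26% |
| 0.7 | 0.95 | 0.3 | 0.480 | 9.62 | 6.94 | 28% |
| 0.7 | 0.90 | 0.4 | 0.280 | 9.68 | 8.22 | 15% |
| 0.9 | 0.85 | 0.5 | 0.073 | 8.68 | 8.36 | 4% |

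The 28% and 4% rows are the extremes of the whole grid. They equal an unadjusted trial of 80/(1 − 0.480) = 154 and 80/(1 − 0.073) = 86 participants instead of 80.

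**3. Chance imbalance.** Split 80 participants 40/40 at random, ignoring the adherence strata (hypergeometric distribution). The arms differ by at least 10 points in baseline undetectable share with probability 26% (u = 0.9) to 50% (u = 0.5), and by at least 15 points with probability 6% to 26%. A 10-point imbalance moves the crude Month 7 difference by 10 × (a − b) points, that is 3.5 (0.85 − 0.5) to 6.5 (0.95 − 0.3).

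**4. Power and type I error, by simulation.** Suppose the intervention raises UDVL from 30% to 60% among those detectable at baseline and leaves a = 0.95 unchanged (20,000 runs per scenario).

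| u | Unadjusted test | Stratified on baseline VL (CMH) |
|---|---|---|
| 0.3 | 50% | 60% |
| 0.5 | 30% | 41% |
| 0.7 | 17% | 23% |

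With no effect, both tests reject in about 5% of runs.

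**5. The detectable subgroup.** At u = 0.7, 0.3 × 40 = 12 per arm are detectable at baseline. At a rate of 30%, the 95% half-width of their arm difference is 1.96 × √(2 × 0.21/12) = 0.37, or ±37 points.

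**The case against.** The strongest reply is that this is an unnamed covariate for a secondary outcome in a condensed article, and that the analysis plan may supply it. The covariate wording is open-ended, and nothing excludes baseline VL. That stands as a reason for low severity, but it does not dispose of the point. The article does choose for UDVL: it fixes the effect measure, picks adherence as the stratifier and writes the adjusted models for adherence. Even if the wording on similar treatment is read to extend modelling to UDVL, covariates are selected by their association with high adherence, so baseline VL has no assured place.

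A reader might infer four stronger things that the article does not support.

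- **That enrichment ignores VL.** Detectable VL is one of the three entry conditions; CD4 was the main proxy, not the only one.
- **That baseline VL enters no analysis.** Clinical markers lists a baseline-to-endline UDVL comparison. The gap is confined to the comparison between arms.
- **That the crude comparison is biased or its test invalid.** Randomisation makes it unbiased on average, its interval already allows for chance imbalance, and the simulated type I error is about 5%. Stratifying on Month 1 adherence may also balance VL in part, by an amount the article does not let one estimate.
- **That undetectable participants dilute the effect and adjustment cures this.** Keeping suppression is a genuine outcome for an intervention meant to maintain adherence. Standardising over baseline VL estimates the same overall risk difference more precisely. Only reporting within groups separates gained from kept suppression, and those figures will be imprecise.

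**Conclusion.** The point holds as one of efficiency and interpretation. The trial will mix adolescents detectable and undetectable at baseline, VL is known for all of them before randomisation, and no stated between-arm UDVL analysis uses it. The comparison remains valid but is less precise than the data allow, and any one realised trial is open to a shift of a few points from chance imbalance.

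The size depends entirely on assumed rates. Over the ranges used, the gain in standard error runs from 4%, which is negligible, to 28%, which is worthwhile. It is small if nearly everyone is undetectable at entry or if baseline status predicts weakly. Power for UDVL was at most 60% in the simulated scenarios even with stratification, so the change does not turn UDVL into a well-powered outcome. As UDVL is secondary, Aim 4 is non-confirmatory and the trial is powered on adherence, this is a minor recommendation that alters no primary conclusion.

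**What to change.** In Analytic approach (Specific Aim 4) and General approach, state that the between-arm Month 7 UDVL risk difference and its 95% interval will be estimated stratified on, or standardised over, pre-randomisation VL status (detectable versus undetectable). Keep the unadjusted difference alongside it if wished.

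Also report Month 7 UDVL by arm within each baseline VL group, as description only, with a note that the detectable group will probably be small and its arm difference imprecise.

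Eligibility, randomisation, visits and sample size stay as they are. Baseline VL is already budgeted and collected in everyone, so the cost is analysis wording, best settled before Month 7 results are seen by arm.

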The study is informed by Self-Determination Theory (SDT), a psychological theory used to improve quality of patient motivation and, consequently, adherence behavior [47–49]. SDT informed one of the WPC-based interventions with adults in China, confirming correlations between key SDT constructs, such as competence, self-regulation, and support [50]. SDT has previously been used as a framework for interventions regarding behavior change with adolescents, particularly surrounding exercise regimens [51–53], as well as one study of adherence to asthma medication [54]. In baseline and endline surveys of the RCT, we will measure the component SDT constructs (perceived autonomy support, relative autonomy index, perceived competence, and relatedness) using validated scales. We have adapted the autonomy support scale to include perceived supportiveness of the WPC and triggered reminders, in addition to support from nurse and physician care providers. In applying the SDT model to adolescents, we expect that we may identify some important differences from adults, and therefore will measure additional items that emerged in our formative work with Chinese adolescents, including family routines, schedule interruptions, and self-efficacy. We will also measure other sources of social support, stigma, and depression, as these have been shown to impact adherence [55, 56].

The study has been approved by the Institutional Review Boards of the University of New England (reference 071316–001), the Institute for Population Health and Development (reference PHAD-2016/SAAV-01), and the Ethics Committee of the National Hospital for Pediatrics in Hanoi (reference VNCH-RICH-16-015).

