### RCT data collection procedures

Once enrolled, RCT participants will provide study data as follows:*Sociodemographic data and SDT constructs*: upon enrollment, all participants will complete a baseline survey with the site coordinator which will cover: age; gender; ethnicity; education; school-going behaviors; family routines; scales for each of the SDT constructs; self-efficacy; stigma; a child depression index; and a strengths and difficulties index.*Continuous adherence data in Months 1–7*: data on WPC openings will be transmitted continuously via 3G cellular network to a central server, which will automatically download data to a password-protected web-based database that investigators can access as needed for analysis. This system will provide adherence data for each participant. We will also collect data on the frequency of reminder messages sent to each participant by type of reminder, for intervention participants only.*Continuous data on signal lapses*: during Month 1, we will investigate all WPC signal lapses lasting ≥ 48 h by phone call to the participant and determine whether a lapse was due to technical failure (battery failure, forwarder malfunction) or behavioral cause (missed dose, intentional non-use).*Device utilization questionnaire*: we will administer a survey on adolescents’ experience using the WPC at the Month 1 visit for all participants.*Monthly check-in questionnaire*: a brief questionnaire will be administered to all participants to collect data on: whether adherence counseling occurred (yes/no); who was responsible for WPC management; and the occurrence of any major life events (including status disclosure).*Month 7 follow-up questionnaire*: a final survey will be administered to all participants at the end of the intervention period, similar to that completed at baseline, with the addition of a brief quantitative and open-ended questionnaire asking about experience with the WPC, including convenience of use, storage, and potential stigma/loss of confidentiality.*Biological samples*: all participants will provide blood samples for CD4 count and VL tests at Month 1 (pre-randomization) and Month 7 (post-intervention period). Standard of care in Vietnam is CD4 count testing every three months and VL testing every six months free of charge to patients, but VL tests are rarely done due to cost. We will try to time enrollment to align with patients’ blood draw schedule such that, in general, no additional blood draws will be necessary for VL or CD4 tests, but some patients may be enrolled at a time when they are not due for a regular CD4 test; these patients will require an extra blood draw for the study at enrollment. All samples will be identified only by the patient’s study ID to ensure confidentiality. Data will be provided to the clinic for addition to participants’ charts in order to inform treatment. All extra testing costs will be paid for by the research project budget.

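### The adjusted adherence model picks extra covariates by their significance with the outcome, does not limit them to baseline, and does not assure a place for the randomisation stratum

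*Protocol article*

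**What the plan says.** In the protocol article, General approach, the main dichotomous outcome is the proportion with at least 95% adherence at Month 7, for which "risk differences and 95% confidence intervals will be calculated". A multivariate regression follows, with high adherence as outcome and arm as primary predictor. It adjusts first for key baseline variables; gender is the only one named. Then comes the selection rule: "Other variables found to be significantly associated with high adherence in bivariate logistic models will be added using forward-stepwise and forced entry techniques". Similar methods are to be used for change in adherence and for CD4.

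Three other places bear on the rule:

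- Pre-intervention period and randomization (Month 1): participants are randomised within strata of Month 1 adherence, cut at 95% on-time doses.
- Study aims and design: "In baseline and endline surveys of the RCT, we will measure the component SDT constructs". The autonomy support scale was adapted to cover how supportive the pill container and its reminders are felt to be.
- RCT data collection procedures: a monthly form records whether counselling took place, and "a final survey will be administered to all participants at the end of the intervention period, similar to that completed at baseline".

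Analytic approach (Specific Aim 4) calls the efficacy analysis non-confirmatory and plans results by baseline-adherence stratum as well as overall.

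**The concern.** The model estimates the effect of the intervention, yet its covariates are settled by looking at the outcome. That has three consequences.

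- With few non-events, which covariates pass the screen is partly chance. A repeat of the same trial could adjust for a different set.
- The sentence before the rule is limited to baseline variables, but the rule itself is not. Endline self-determination scores and counselling records are plausible candidates: they may well be associated with adherence, and the intervention is meant to change them. Adjusting for them removes part of the effect being estimated.
- The stratification factor is a covariate that the design itself marks as prognostic. It enters only if the analyst counts it among the key baseline variables or if it passes the screen.

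At stake is the adjusted estimate, for this outcome and for the continuous outcomes that follow the same approach. It is preliminary evidence that may inform a larger study.

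**Working it through.** **Inputs** (Sample size and power considerations): "We will recruit 80 adolescent patients, 40 per study arm"; "two-sided alpha of *p* = 0.05"; "We will have a minimum of 80% power to detect down to a 29 percentage-point difference in proportions achieving ≥ 95% adherence"; and, from the earlier study in Chinese adults, "proportions achieving ≥ 95% adherence were 87.3% versus 51.8%, in intervention versus control patients after six months of the intervention".

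**1. The plan's own figure.** Take the control rate as 51.8% and the intervention rate as 51.8% + 29 = 80.8%, with n = 40 per arm and a pooled normal approximation.

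- Mean rate = (0.808 + 0.518)/2 = 0.663.
- z = [√40 × 0.29 − 1.96 × √(2 × 0.663 × 0.337)] / √(0.808 × 0.192 + 0.518 × 0.482) = (1.834 − 1.310)/0.636 = 0.82.
- Power = 79.5%, so the stated 80% is reproduced to within rounding and these rates are a fair basis for the next step.

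**2. Non-events** = 40 × (1 − p_control) + 40 × (1 − p_intervention), with full follow-up.

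| Control vs intervention | Non-events |
|---|---|
| 51.8% vs 80.8% (control rate plus 29 points) | 40 × (0.482 + 0.192) = 26.96 |
| 51.8% vs 87.3% (earlier study's rates) | 40 × (0.482 + 0.127) = 24.36 |
| 58.3% vs 87.3% (29 points below the earlier intervention rate) | 40 × (0.417 + 0.127) = 21.76 |

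An assumed 10% dropout in the first row gives 36 × 0.674 = 24.3. Lower adherence raises the count: an assumed 40% vs 69% gives 40 × (0.60 + 0.31) = 36.4.

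**3. Parameters these counts support.** At the common guide of 10 per parameter (a convention, not a figure in the documents), 21.76 to 26.96 non-events support 2.2 to 2.7 parameters including arm. At 5 per parameter they support 4.4 to 5.4. The rule sets no limit.

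**4. Selection with baseline noise only.** Simulated trials: n = 80, about 27 non-events, 12 candidates unrelated to outcome, bivariate screen at p < 0.05, forward entry at p < 0.05 with arm kept in, 1,500 runs. The number of candidates and the thresholds are assumptions.

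- At least one noise covariate was kept in 34% of runs. As a cross-check, the screen alone would pass at least one in about 1 − 0.95^12 = 46%; the second test lowers this.
- The median log odds ratio for arm was 1.40 unadjusted and 1.44 after selection. Rejection of no effect was 78.1% and 78.2%.

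Selection among baseline variables therefore makes the composition of the model haphazard, but on average does not move the arm effect much.

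**5. Selection with a post-randomisation mediator among the candidates.** Same procedure, plus one variable that the intervention raises by 0.8 SD and that raises the log odds of high adherence by 1.0 per unit, with a direct arm effect of 0.75. All three values are assumed; mean non-events were 36.

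- The mediator was selected in 96% of runs.
- The median log odds ratio for arm fell from 1.27 to 0.80, and rejection of no effect from 82% to 31%.

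This shows the mechanism. Its size depends on the assumed strengths.

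**The case against.** - **The main result is untouched.** This is so. The risk difference comes first and involves no selection, and the whole efficacy analysis is labelled non-confirmatory. A reader might infer that the trial's headline estimate is at risk; the documents do not support that.
- **The added variables may mean other baseline variables.** This is a natural reading, since the preceding sentence concerns baseline variables, and psychosocial constructs have their own correlations and exploratory path analysis. A reader might infer that endline mediators will be adjusted for. The protocol never says so; it only fails to exclude them. The charge is loose wording with a harmful possible reading.
- **Baseline adherence may already be covered.** The list of key baseline variables is open, and results by stratum are planned. So the stratum is not shown to be omitted; it is merely not assured.
- **The two entry techniques may not compete.** They could mean a forced core plus stepwise additions, so two rival adjusted results cannot be assumed.
- **False positives are not inflated.** With baseline candidates only, simulated type I error for arm stayed near 5 to 6%. No result on interval coverage was produced, so unreliable confidence intervals are not shown.
- **Details belong in the analysis plan.** A closed list, threshold or cap may well be there. But choosing covariates by outcome significance is a rule that this article states, and an analysis plan that followed it would carry it forward.

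**Conclusion.** The point stands for the secondary, non-confirmatory adjusted model. The stated rule is an inferior way to adjust a treatment effect: it lets the outcome data choose the covariates, does not restrict them to baseline, and does not guarantee the randomisation stratum.

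The supported size is modest. About 22 to 27 non-events are expected at the protocol's planning rates with full follow-up, and more if these adolescents, selected for adherence challenges, adhere less well. Noise covariates enter in roughly a third of simulated trials under the assumed 12 candidates and 0.05 thresholds. If post-randomisation measures were admitted, attenuation is the likely direction when they act beneficially, though conditioning on such variables can bias either way. The documents give nothing from which to fix the amount, so no particular loss in percentage points should be read into this.

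**What to change.** For the model that estimates the arm effect, and likewise for change in adherence and CD4:

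- Remove the bivariate screen and stepwise entry.
- Pre-specify arm, baseline adherence, and at most one further baseline covariate such as gender. Enter baseline adherence either as the randomisation stratum or as continuous Month 1 adherence. Using both would enter the same measurement twice and make four parameters. Three parameters give 21.76/3 = 7.3 to 26.96/3 = 9.0 non-events each, close to the guide of 10.
- For the dichotomous outcome, report an adjusted risk difference with 95% CI, on the same scale as the unadjusted result.
- State that only variables measured before randomisation may enter.
- Keep screening and post-randomisation variables for the exploratory analysis of correlates and the path analysis already planned, labelled as such.

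The cost is a change of wording, with no change to data collection. The downside is less freedom to add covariates later.
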